## 13.2 Exploratory Objectives

**Exploration Analysis:** The unique aspects of this proposed intervention, related to development of an adaptive approach to smoking cessation treatment is expected to provide a rich database for subsequent exploratory analyses. Accordingly, we will conduct a number of such analyses primarily – but not restricted to – investigating putative associations between primary outcome measures of abstinence, compliance, attrition, with numerous demographic, ecological, clinical, physical, and psychological factors (including but not limited to: age, gender, race, income, education, insurance status, nicotine dependence, physical and psychiatric comorbidity), measured and tested variously across, between, and within conditions. As we are proposing these studies as exploratory, a-priori assumptions on outcomes, although not excluded, are also not mandated. Modeling strategies and details will necessarily be assessed through study outcomes with questions and requisite data not outlined herein.

### 13.5.1 Key Exploratory Objective Analysis

**Patient demographics and other baseline characteristics:** The unique aspects of this proposed intervention, related both to development of an adaptive approach to tobacco use treatment and as an exemplar of a large scale translational study into the feasibility and efficacy of service engagement and delivery, is expected to provide a rich database for subsequent exploratory analyses. Accordingly, we will conduct a number of such analyses primarily, but not restricted to, investigating putative associations between primary outcome measures of abstinence, compliance, and attrition with numerous demographic, ecological, clinical, physical, and psychological factors (including but not limited to: age, gender, race, income, education, insurance status, nicotine dependence, physical and psychiatric comorbidity), measured and tested variously across, between, and within conditions. As we are proposing these studies as exploratory, a-priori assumptions on outcomes, although not excluded, are also not mandated. Modeling strategies and details will necessarily be dictated by the structures of both the questions and the requisite data and, hence, are not outlined herein.

**Assessment of potential moderators of primary effect:** The following constructs will be assessed as potential predictors of abstinence: demographics (age, gender, race, education), smoking history and heaviness, financial status, dependence (measured by FTND), urge rating (measured by MPSS), depression (measured by PHQ-2), anxiety (measured by GAD-2), alcohol use (measured by AUDIT-C), stress (measured by PSS-4), and self-efficacy questions. Constructs that demonstrate an association with abstinence will be analyzed for potential moderation. Tests for differential associations of effects of baseline characteristics by randomization status on week-12 smoking abstinence will be based on interaction terms crossing randomization status (group) with the tested (putative) baseline predictor. Significance of the estimated coefficient associated with the interaction term would indicate that the effect of the tested predictor on abstinence varied differentially by treatment assignment. For each baseline predictor, we hypothesize that baseline will be equivalent across all randomized arms. In a second series of tests, the above protocol will be used to test for differential rates of change in abstinence associated with putative constructs (scales): urge (MPSS-2), stress (PSS-4), depression (PHQ-2), anxiety (GAD-2). As above, the primary test statistic will be based on interaction term crossing the tested scale with group.

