#### Exploratory Objectives

6. To assess potential baseline (pre-intervention) predictors of abstinence including self-reported dependence, stress, anxiety, depression, alcohol and drug use, and self-efficacy. If a baseline variable is found to be associated with abstinence, it will be further assessed as a moderator of abstinence.
7. To assess change in self-reported measures at baseline (pre-quit) to 2- and 12-weeks post TQD on repeated standardized measures of nicotine dependence, stress, anxiety, depression, alcohol and drug use, and self-efficacy. If a measure is found to change significantly from baseline to a post quit time point, it will be assessed as possible mediator of abstinence outcomes.
8. To compare phone-assessed non-standardized single item questions on urges, withdrawal, motivation to quit smoking or remain abstinent, and confidence in ability to quit or remain abstinent at 1, 2, 6, 12, 26 and 52 weeks post-TQD. If a measure is found to change significantly from baseline to a post quit time point, it will be assessed as a possible mediator of abstinence outcomes. Phone assessments will be compared at specific time points and also across multiple time points using multi-level modeling.

9. To compare baseline scores on anxiety, depression, and stress for their effect on allocation to Responder or Non-Responder status in the adaptive and standard treatment arms.
10. To conduct cost-benefit analyses on allocation to adaptive vs standard treatment from the perspective of multiple stake holders: smokers, healthcare systems (clinics/hospitals), insurance companies, and employers.

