**Analysis of Primary Outcome:** The primary outcome measure is biochemically confirmed 30-day continuous abstinence at the 12-week post-Target Quit Day (TQD) confirmed by carbon monoxide (CO) breath testing with CO < 7ppm. The study hypothesis is that adaptive treatment arms of the study will show higher smoking abstinence at 12-weeks post-quit attempt vs. non-adaptive treatment. An intent-to-treat approach will be taken to analyze primary outcomes such that all subjects who are enrolled in the study will be included in the primary analysis of outcomes. Outcomes will be analyzed using generalized linear regression modeling using an ANOVA-based design. An alpha criterion of 0.05 (two-tailed) will be used in all comparisons. For a conservative estimation of abstinence, subjects lost to follow-up after the point of randomization will be counted as non-abstinent. Following this, however, a sensitivity analysis will be conducted to determine the impact of this assumption, using multiple imputation procedures that model smoking outcomes in terms of “missingness” and smoking at previously observed time-points.

**Secondary smoking outcomes:** Analysis of secondary smoking outcomes will include comparison of abstinence rates in Adaptive vs. Non-Adaptive groups via self-reported 7 and 30-day continuous abstinence and number of cigarettes smoked per day at 2- and 12-weeks post TQD. Secondary smoking outcomes will be assessed using intent-to-treat principles with use of multiple imputation to account for missing data.

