**Varenicline-Based Treatment (secondary outcome):** Power calculation for Varenicline Based Adaptive treatment vs. Varenicline Standard Treatment is based on abstinence rates observed in prior P50-funded trials as well as other published studies. To estimate the effect of adaptive treatment, a critical consideration is that 4 week Varenicline pre-cessation treatment without adaptation was superior to starting 1 week prior to quit day (Hajek et al 2011). Abstinence rate were 20.8% 1-week pre-quit start time. Hajek further showed that for participants starting 4 weeks prior to the Quit day, 35.4% of participants showed >50% reduction in cigs/day with an abstinence rate of 66.7% whereas 64.6% of participants failed to show >50% reduction in cigs/day and had an abstinence rate of 22.6%. The weighted average of these groups = 38.2%. Sample size calculation using **38.2% vs. 20.8%** with 2-tail test with continuity correction assuming  $p = 0.05$  and power = 80%, yields a minimum sample size of **208** within the Varenicline arm alone. This study is designed with 150 in the Varenicline arm and so it underpowered to reach this secondary outcome.

Version Date: 02/26/2020

**Full Sample (Primary Outcome):** Based on these calculations, a sample size of 300 for each of these comparisons should be sufficient to demonstrate significant differences between randomized arms (150 vs. 150). The Primary Outcome is a comparison of 12-week post-TQD smoking abstinence across the study sample (N=300). As stated above, the nicotine patch arm will require n=298 to reach significance, and the varenicline arm will require n=208 to reach significance. Neither arm (150 each) is powered to reach significance. The two arms together (n=300) are powered to reach primary outcomes. For the control group (nicotine patch arm = 26.0%; varenicline arm = 20.8%), an equally weighted sample would result in an abstinence rate of **23.4%**. For the adaptive treatment group (nicotine patch arm = 41.2%; varenicline arm = 38.2%), an equally weighted sample would result in abstinence rate of **39.7%**. A sample size calculation using 2-tail test with continuity correction assuming  $p = 0.05$  and power = 80% results in sample size of **248**. With 300 participants this study as power of 87% power for showing significant results on our primary outcome.

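### Testing a baseline factor as a moderator only after it shows an association with abstinence can screen out factors that change the treatment effect

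*Protocol*

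**What the plan says.** Section 13.5.1, in the paragraph on potential moderators of the primary effect, names demographics, smoking history and heaviness, financial status, FTND, MPSS, PHQ-2, GAD-2, AUDIT-C, PSS-4 and self-efficacy. It then says: "Constructs that demonstrate an association with abstinence will be analyzed for potential moderation". The next sentence defines the test: effects on week-12 abstinence "will be based on interaction terms crossing randomization status (group) with the tested (putative) baseline predictor".

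The Exploratory Objectives in Section 3.1 put the rule as an explicit condition: "If a baseline variable is found to be associated with abstinence, it will be further assessed as a moderator of abstinence". The objectives table in Section 6 repeats it. For the significance level, the protocol says: "An alpha criterion of 0.05 (two-tailed) will be used in all comparisons".

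No section commits to testing the interaction for a listed construct that fails the first step. The second series of tests in Section 13.5.1 (urge, stress, depression, anxiety) follows the same procedure and concerns rates of change, so it does not clearly lift the condition.

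**The concern.** The first step asks whether a factor predicts abstinence. The second asks whether the difference between adaptive and standard treatment varies with that factor. These are different quantities, and a factor can have a large interaction with no association once the arms are combined. This happens when it lowers abstinence under one strategy and raises it under the other. Followed as written, the plan would drop such a factor before the test that Section 13.5.1 itself defines as the test of moderation.

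The pattern is not far-fetched on the protocol's own account. Section 3.2 names depression among the characteristics with evidence as predictors of relapse. Section 5.2 says that bupropion gave higher abstinence in depressed smokers in some studies, and only the adaptive arms give active bupropion. Two features weaken the example: only adaptive non-responders receive active bupropion, and Section 9.2 excludes a PHQ-2 score of 3 or above.

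At stake is what the trial can say about differences in response between kinds of smoker. The comparison of adaptive with standard treatment is not at stake.

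**Working it through.** **Inputs from the protocol.** The sample size section gives control abstinence of 26.0% (patch) and 20.8% (varenicline), and adaptive abstinence of 41.2% and 38.2%. Equal weighting gives (26.0 + 20.8)/2 = 23.4% and (41.2 + 38.2)/2 = 39.7%. Allocation is 150 vs 150, and alpha is 0.05 two-sided.

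**Assumptions, not in the protocol.** The factor is binary and splits each arm 50/50, so there are 75 participants per cell. The first-step association is tested pooled over arms at two-sided 0.05. The subgroup rates are chosen so that the arm averages stay at 23.4% and 39.7%.

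**The plan's own figure.** The protocol gives no power for the moderator analysis. Its primary-outcome figures serve only to anchor the rates. For 39.7% vs 23.4% it states N = 248 for 80% power and "With 300 participants this study as power of 87% power for showing significant results on our primary outcome". A two-proportion calculation without continuity correction gives N = 254 and 86.3% power at 300, close to both. With the continuity correction that the text names, it gives N = 278 and about 83%; that is a separate matter.

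**One case by hand.** Take control 33.4%/13.4% and adaptive 29.7%/49.7% at the two levels of the factor.

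- Treatment effects: 29.7 - 33.4 = -3.7 points and 49.7 - 13.4 = +36.3 points.
- Pooled abstinence by level: (33.4 + 29.7)/2 = 31.55% and (13.4 + 49.7)/2 = 31.55%. There is no pooled association to find.
- Interaction on the log-odds scale: [logit(0.497) - logit(0.297)] - [logit(0.134) - logit(0.334)] = (-0.012 + 0.862) - (-1.866 + 0.690) = 2.03.
- Variance: the sum of 1/(75·p·(1 - p)) over the four cells = 0.060 + 0.115 + 0.064 + 0.053 = 0.292, so SE = 0.54.
- Approximate power: Φ(2.03/0.54 - 1.96) ≈ 0.96.

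**Simulation.** There were 200,000 trials per pattern. The first step is a two-sided 0.05 test of factor against abstinence over both arms. The second is a two-sided 0.05 Wald test of the interaction log odds ratio.

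| Control rates by level | Adaptive rates by level | Treatment effects (points) | Passes first step | Interaction power, tested directly | Interaction power, with first step |
|---|---|---|---|---|---|
| 33.4% / 13.4% | 29.7% / 49.7% | -3.7 / +36.3 | 4.1% | 97.2% | 4.0% |
| 31.4% / 15.4% | 31.7% / 47.7% | +0.3 / +32.3 | 4.3% | 86.6% | 3.7% |
| 29.4% / 17.4% | 33.7% / 45.7% | +4.3 / +28.3 | 4.5% | 62.6% | 2.7% |
| 23.4% / 23.4% | 29.7% / 49.7% | +6.3 / +26.3 | 46.4% | 37.3% | 17.2% |
| 23.4% / 23.4% | 23.4% / 56.0% | 0 / +32.6 | 87.4% | 77.7% | 67.7% |
| 23.4% / 23.4% | 19.7% / 59.7% | -3.7 / +36.3 | 97.0% | 92.1% | 89.3% |

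The first and last rows have identical treatment effects. The screen removes nearly all the power in one and about 3 points in the other. The difference is whether the factor's association with abstinence under control offsets its association under adaptive treatment.

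**Cost of dropping the screen.** Counting smoking history and heaviness as one, Section 13.5.1 lists 13 constructs. At 0.05 each, and if independent, the chance of at least one false positive is 1 - 0.95^13 ≈ 0.49.

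**The case against.** A reader might infer that the rule removes the qualitative interactions, those in which adaptive treatment helps one group and harms another. The figures do not support that. A true reversal of the treatment effect over a flat control rate passes the first step in 97% of trials. What the screen fails on is cancellation of the factor's association across arms, whether or not the treatment effect changes sign.

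It can also be said that the fall from 97% to 4% is a chosen worst case. That is fair: the rates were set to make the pooled association exactly zero, and nothing in the protocol says that any construct behaves so. The range has to be given, and other patterns lose far less.

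The objective is worded first as a search for predictors of abstinence, with moderation as a follow-on, so selecting prognostic factors is partly what it is for. This stands as to the predictor analysis, and one should not claim that the protocol's declared aim is to find out for whom adaptive treatment works. It does not justify using the predictor result to decide which interactions are examined.

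Section 13 leaves further exploratory analyses open in general terms, so it would be too strong to say that a screened-out factor can never be tested. No section promises that it will be, however.

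Finally, the screen limits the number of tests. That is a real benefit, but full reporting under an exploratory label deals with the problem without selecting on the wrong quantity.

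**Conclusion.** The point holds in limited form. The condition appears in three places and is fixed by the protocol, so an analysis plan that followed it would carry it forward. It selects on prognosis rather than on difference in treatment effect, and it can screen out real moderators. At the protocol's arm averages the loss of power for the interaction ranges from about 3 points (92% to 89%), through 10 points (78% to 68%), to nearly all of it (97% to 4%).

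These sizes rest on a 50/50 factor, assumed subgroup rates, and a first step pooled over arms at 0.05. Pooling is the natural reading because no arm is named. If the association were instead sought within each arm, a reversing factor could pass.

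The matter is minor. The analyses are exploratory, and the primary comparison and its sample size are untouched.

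**What to change.** Delete the main-association condition from the Exploratory Objectives in Section 3.1, the objectives table in Section 6 and the moderator paragraph in Section 13.5.1. Fit the arm-by-construct interaction for every construct listed in Section 13.5.1, whatever its association with abstinence. Report every estimate with its confidence interval, labelled exploratory. The predictor analysis can stay as a separate item.

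This takes about 13 interaction models instead of a subset, and no new data, visits or participants. The downside is multiplicity: with roughly a 49% chance of at least one false positive if the tests are independent, the text should say that no single significant interaction will be read as confirmatory.

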**Economic Analysis:** An economic analysis of Adaptive vs. Non-Adaptive pharmacotherapy will be conducted. [name], PhD, MBA, a Duke University Health Economist with expertise in cost-benefit analysis for healthcare system program operation will conduct this analysis and oversee prospective data-collection on cost and time for all necessary TSCP operations to generate a prospective economic analysis of adaptive vs. non-adaptive treatment to identify cost-benefit outcomes from the perspective of smokers, healthcare systems, insurance companies, and employers. Cost assessments of adaptive treatment will include: 1) Descriptive statistics to compare overall cost of medications for adaptive vs. non-adaptive treatment. 2) ANOVA modeling to analyze cost of medications per abstinent smoker comparing adaptive vs. non-adaptive treatment. 3) ANOVA modeling to analyze the cost of prescribed medications as related to medication non-adherence and attrition. 4) Mediation analysis on how randomization status affects medication adherence and how that relationship is mediated by income.

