| Exploratory | To conduct a cost-benefit analyses on allocation to adaptive pharmacotherapy algorithm vs. standard-of-care treatment from the perspective of multiple stake holders: smokers, healthcare systems (clinics/hospitals), insurance companies, and employers.                                                                                                                                                                                     | Biochemically confirmed abstinence measures as well as phone measures, demographic measures and financial questions and work questions (see Appendix 3 and 12)                                                                                        | See Section 13 |
| Feasibility | Demographics of patients at DSCP and Duke CSC                                                                                                                                                                                                                                                                                                                                                                                                  | Demographic variables assessed                                                                                                                                                                                                                        | See Section 13 |
| Feasibility | Medications used                                                                                                                                                                                                                                                                                                                                                                                                                               | Medication selection at randomization                                                                                                                                                                                                                 | See Section 13 |

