#### 7.1.6. Randomization

Randomization will occur through an open source randomization program “Research Randomizer” developed for randomization of subjects in psychology and medication trials. This can be found at <https://www.randomizer.org/>. To simulate clinical treatment, the study design provides for subject choice into one of two arms: Varenicline-based treatment (n=150) or Nicotine Patch-based treatment (n=150). Once the initial treatment arm is chosen, subjects will be randomized to Varenicline adaptive pharmacotherapy (n=75) vs. Varenicline alone (n=75), or similarly nicotine patch adaptive treatment (n=75) vs. nicotine patch alone (n=75).

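### The economic plan applies ANOVA to medication cost per abstinent smoker, a ratio of arm totals with no valid participant-level form

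*Protocol*

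**What the plan says.** The Economic Analysis paragraph of Protocol Section 13.5.1 aims to "identify cost-benefit outcomes from the perspective of smokers, healthcare systems, insurance companies, and employers". It lists four cost assessments. Item 1 is "Descriptive statistics to compare overall cost of medications for adaptive vs. non-adaptive treatment". Item 2 is "ANOVA modeling to analyze cost of medications per abstinent smoker comparing adaptive vs. non-adaptive treatment". Item 3 models prescribed-medication cost against non-adherence and attrition, and item 4 is a mediation analysis of adherence.

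The paragraph does not define cost per abstinent smoker for an individual, does not say how the costs of non-abstinent participants enter it, and names no method for a ratio.

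Three other statements bear on the point:
- The objective in Section 6 is "To conduct a cost-benefit analyses on allocation to adaptive pharmacotherapy algorithm vs. standard-of-care treatment", so the comparison of interest is by allocation. It is listed there as exploratory.
- For the primary outcome, Section 13.4 (Statistical Hypothesis, Model, and Method of Analysis) says that "all subjects who are enrolled in the study will be included in the primary analysis of outcomes".
- The same section states that "An alpha criterion of 0.05 (two-tailed) will be used in all comparisons". Read literally, item 2 would yield a significance test.

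**The concern.** ANOVA by arm needs one value per participant and a within-arm variance. Cost per abstinent smoker supplies neither, because it is a single number for each arm. The analyst would have to invent a participant-level version, and each obvious candidate fails:
- Medication cost among abstainers only: this selects on a post-randomization outcome that treatment is expected to change, and omits what was spent on those who did not quit.
- Non-abstainers set to zero: failures are treated as free, so an arm with more quitters has a higher mean cost.
- Each person's cost divided by the arm's abstinence rate: the estimated denominator is treated as known, so the standard error is wrong.

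The first is the likeliest in practice. It would give a difference between self-selected groups in which the gain in abstinence plays no part. The results are meant to inform health systems, insurers and employers, who need to know what an additional quitter costs.

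**Working it through.** The protocol gives no economic figure to reproduce. The check uses its planning rates to see what an abstainers-only ANOVA would compare, and sets that against the ratio named in the text.

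**Inputs.** From Section 13.4 (Sample Size Calculation): abstinence on standard treatment 26.0% (patch) and 20.8% (varenicline), mean 23.4%; on adaptive treatment 41.2% and 38.2%, mean 39.7%; 150 participants per strategy. Non-responders are 58.8% of adaptive patch users (28.3% abstinent with bupropion; responders 59.2%) and 64.6% of varenicline pre-quit users (22.6% abstinent; responders 66.7%). The last two abstinence rates come from a study without added bupropion. From Section 10.2, active treatment lasts 16 weeks (adaptive, either drug), 13 weeks (standard varenicline) or 12 weeks (standard patch). Bupropion for non-responders lasts 13 weeks.

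**Who would enter.** Adaptive: 150 × 0.397 = 59.6. Standard: 150 × 0.234 = 35.1. Together 94.7 of 300 (31.6%). About 205 would be left out, in unequal shares: 60.3% of adaptive and 76.6% of standard.

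**Change in case mix, patch.** Expected adaptive abstinence is 0.412 × 0.592 + 0.588 × 0.283 = 0.4103. The non-responder share of abstainers is 0.588 × 0.283 / 0.4103 = 40.6%, against 58.8% of the arm. The share receiving bupropion is thus low by 1 − 0.406/0.588 = 31%. For varenicline the corresponding share is 0.646 × 0.226 / 0.3821 = 38.2%, against 64.6%.

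**When adaptive is cheaper per abstainer.** Cost per abstainer = mean cost per randomized participant / abstinence rate. Adaptive is lower when its mean cost relative to standard is below 0.397/0.234 = 1.70 (patch 0.412/0.26 = 1.58; varenicline 0.382/0.208 = 1.84). An abstainers-only comparison shows adaptive dearer as soon as the ratio among abstainers exceeds 1.00.

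**Illustration.** Assumptions: bupropion's weekly price is q times that of the base drug; the base drug's weekly price is the same in both arms (this ignores the higher patch strength that Section 10.2 allows only in the adaptive arm); everyone uses the full course. Costs are in base-drug weeks.

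- Patch, whole arm: (16 + 13q × 0.588)/12, divided by 0.412/0.26. Abstainers only: (16 + 13q × 0.406)/12.
- Varenicline, whole arm: (16 + 13q × 0.646)/13, divided by 0.382/0.208. Abstainers only: (16 + 13q × 0.382)/13.

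| Adaptive/standard ratio | q = 0 | q = 0.25 | q = 0.5 | q = 1 |
|---|---|---|---|---|
| Patch, cost per abstainer, whole arm | 0.84 | 0.94 | 1.04 | – |
| Patch, mean cost, abstainers only | 1.33 | 1.44 | 1.55 | – |
| Varenicline, cost per abstainer, whole arm | 0.67 | 0.76 | 0.85 | 1.02 |
| Varenicline, mean cost, abstainers only | 1.23 | 1.33 | 1.42 | 1.61 |

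The two analyses disagree in direction for q below about 0.39 for patch, from (12 × 0.412/0.26 − 16)/(13 × 0.588), and below about 0.94 for varenicline, from (13 × 0.382/0.208 − 16)/(13 × 0.646).

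For patch at q = 0.25, mean cost is 17.91 weeks (adaptive) against 12. Cost per abstainer is 17.91/0.412 = 43.5 against 12/0.26 = 46.2, and the incremental cost is 5.91/0.152 = 38.9 weeks per additional abstainer. Abstainers-only ANOVA would report 17.32 against 12.

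**The case against.** The strongest reply is that restriction to abstainers is inferred. The text does not say so, and if the quantity is read as a ratio of arm totals, the fault is only a mismatch of method, with no post-randomization selection and no lost costs. This is right, and the mismatch is therefore the point made here. The abstainers-only consequences are conditional on that reading.

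Second, the costs of treatment failures are not missing from the economic plan. Item 1 compares overall medication cost, item 3 relates cost to attrition, abstinence is analysed in all enrolled participants, and a health economist is to conduct the work. This also stands. But item 1 is descriptive and not linked to abstinence, and item 2 is the only listed assessment that joins cost to abstinence.

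Third, the objective is exploratory in Sections 3.1 and 6, although Section 13.4 (Sample Size Calculation) mentions economic outcomes among the secondary ones. Section 13.5.1 says that exploratory modelling details are not set out there, and an unseen analysis plan may supply them. That would excuse silence. Here, however, the protocol names both a quantity and a method, and the two do not fit.

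Fourth, adaptive treatment may truly cost more per person, so a positive difference is not in itself wrong. This is correct: the disagreement in direction is with average cost per abstainer, and every price used is assumed.

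**Conclusion.** The point holds in a limited form. Item 2 prescribes a method that cannot validly be applied to the quantity it names. Run on abstainers, it would drop about 68% of participants at the planning rates and would not answer the objective, which concerns allocation. Whether the direction would actually reverse depends on prices and adherence that the protocol does not give.

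Three stronger conclusions that a reader might draw are not supported:
- That the plan restricts the analysis to abstainers and so breaks the randomization. The text leaves the population of item 2 unstated.
- That adaptive-arm cost would be understated by 31%. That figure is the shortfall in the share of patch users receiving bupropion. On the assumptions in the illustration, adaptive patch drug cost is understated by about 3% at q = 0.25 (17.32 against 17.91), 6% at q = 0.5 (18.64 against 19.82) and 10% at q = 1 (21.27 against 23.64). This bias makes adaptive look cheaper and so works against the larger one from omitting failures. The abstainers-only ratios tabulated already net the two.
- That the trial's main result is at risk. The primary analysis does not depend on item 2.

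The protocol carries 41.2% forward for adaptive patch where its own weighted average is 41.0%. Using 41.0% moves the pooled threshold only from 1.70 to 0.396/0.234 = 1.69.

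**What to change.** Replace item 2 with an analysis of all randomized participants that reports (a) total medication cost divided by the number abstinent at week 12 in each arm, and (b) the difference in mean medication cost divided by the difference in week-12 abstinence. Give bootstrap or Fieller confidence intervals, and adjust or stratify for the choice of varenicline or patch. Net-benefit regression over a range of values per additional quitter is an equally good alternative, and is more stable if the difference in abstinence proves small. If ANOVA is kept, apply it to medication cost in all randomized participants, which would also give item 1 an inferential counterpart.

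The cost is a rewritten sentence and a little more analysis work. Medication cost, allocation and week-12 abstinence are already to be collected, so no new data are needed.
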